### Measurements

Missing data will not be an issue, as the survey is conducted through LimeSurvey, where all questions are mandatory and cannot be skipped by participants.

To be included in the data analysis, participants must have completed all three measurement points and answered all questionnaires.

T1: First measurement: After the participant had signed the informed consent, the initial score for this outcome was assessed.T2: Second measurement: POST Up to 6 weeks after the second measurement, the second measurement of the same variable was carried out.T3: Third measurement: POST Up to 6 months after the second measurement, the third measurement of the same variable was carried out.

[Time Frame: Baseline up to 30 weeks]

Primary Outcome Measure:

Change Quality of Life (measured by KIDSCREEN-27).Change Emotional and Behavioral Problems (measured by SDQ).Change Emotional Competences (measured by EAQ-30).Change Self-concept (measured by CAG)Change Coping (measured by SPSI-R).Change Social Skills (measured by CHASO).

Secondary Outcome Measure:

Change Threat of disease (measured by BIP-Q)Change Psychoeducation Diabetes

Psychoeducation of the disease: the ECODI Diabetes knowledge scale will be used to assess this variable [79]. This scale consists of 25 items and four dimensions: basic knowledge and self-care, laboratory values, diet and physical exercise. It is a scale that is corrected by the number of hits and misses.

[Time Frame: Start of the game and during the game]

Change Resilience (measured by CD-RISC).

Other Pre-specified Outcome Measures:

Glycaemic control

HbA1c: It will be used to evaluate the glycemic control of the diabetic patient in endocrinology diseases.

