The phase encompassing the evaluation of the variables of interest, T1-T2-T3, will take place through the survey platform of the Universitat de València, Limesurvey, from September 2024 to the end of February of 2027. The response platform for the questionnaire battery includes a consent form for anonymous participation in the study. In this platform, informed consent will be obtained from the parents or legal guardians of the participants, as well as from the minors themselves, ensuring that all are informed about the anonymity and confidentiality of their data, confirming that their participation in the study is voluntary.

To access and play the *emoTICare serious game* online for six weeks (one week per mission of the game), participants will be provided with a link at the end of the evaluation survey conducted at T1. This *serious game* contains six distinct areas, each designed to be completed within a maximum of one week, thus allowing sufficient time to progress at different paces. During the period in which the adolescents are completing the *serious game*, an email address and a mobile phone number will be made available for participants to contact in case they need assistance (see Table 1).

**Table 1 pone.0325763.t001:** Intervention timeline.

				Timeline (in months)																															
	2024							2025												2026												2027			
	Jun	Jul	Aug	Sep	Oct	Nov	Dec	Jan	Feb	Mar	Apr	May	Jun	Jul	Aug	Sep	Oct	Nov	Dec	Jan	Feb	Mar	Apr	May	Jun	Jul	Aug	Sep	Oct	Nov	Dec	Jan	Feb	Mar	Apr

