### Data analysis

In the present study, the per-protocol analysis (PP) approach was utilized to evaluate the effectiveness of the treatment and the management of missing data. This method includes only participants who fully adhered to the study protocol, ensuring that the results reflect the true efficacy of the intervention under ideal conditions. Participants will be included in the main analyses only if they have completed the treatment as per the protocol, that is to say, if they have adhered to all instructions without significant interruption. Participants who withdraw or fail to complete the treatment will be excluded from the analyses. This methodological decision is underpinned by the principle of minimizing potential bias from missing data, thereby ensuring that the results of the study accurately reflect the outcomes of participants who adhered to the treatment protocol. To address the issue of missing data during follow-up or treatment, predefined procedures will be implemented. The last observation carried forward (LOCF) imputation method will be employed to address missing data, with the last available measurement being utilised to complete the missing values. Furthermore, sensitivity analyses will be conducted to assess the impact of missing data on the study outcomes. These procedures are designed to minimise data loss, maintain the internal validity of the study, and ensure the robustness of the results.

Several statistical analyses will be performed to determine the effectiveness of *emoTICare*. As a first step, chi-square tests and t-tests were performed to examine potential differences between the control and experimental groups in key demographic and clinical variables (e.g., age, gender, disease duration). Although randomization is expected to ensure comparability, these tests were conducted to verify baseline equivalence. Propensity Score Matching (PSM) was not used to adjust for baseline differences, as the study followed a randomized controlled design.

Additionally, chi-square tests will compare the number of participants who withdraw from the experimental group with those who withdraw from the control group, ensuring no significant differences exist.

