Secondly, incidental sampling may hinder the generalization of the program’s results, as the sample may not fully represent the wider population of adolescents with Type 1 Diabetes. Thirdly, the online and remote format of the evaluation process, along with the use of the emoTICare program, may present challenges in ensuring proper completion, potentially increasing the likelihood of experimental mortality. Moreover, the online format could impact participant engagement, as the lack of direct interaction may lead to decreased attention or motivation. This is particularly relevant as maintaining participant motivation throughout the study period is a challenge in long-term interventions, and participants may experience fatigue or loss of interest over time. Additionally, biases in self-reported data could arise, as participants might provide socially desirable answers or misinterpret the questions, affecting the accuracy of the data. Conversely, per-protocol analysis (PP) provides a clear understanding of the potential benefits of treatment by focusing on subjects who have completed their assigned treatment regimen. However, it is limited in that it does not account for real-world challenges to adherence in real-world settings.

A further limitation of this study is the absence of specific data on the incidence of type 1 diabetes in individuals under 16 years of age. Instead, the incidence in individuals under 15 was used as a reference. It is acknowledged that this may result in under- or overestimation, owing to the exclusion of data from 15–16-year-olds. It is also noted that, given the relatively narrow additional age span (one year), any deviation in incidence is unlikely to significantly affect the overall power or feasibility estimates of the study. Incidence figures for individuals under 15 years are extensively utilised in international diabetes surveillance and are regarded as robust and comparable across populations. Given that the majority of the target population falls within the 12–14 age range, it was considered reasonable to use incidence data for individuals under 15 years as a proxy for estimating the expected number of eligible participants. Furthermore, the incidence of type 1 diabetes between ages 15 and 16 does not markedly deviate from that observed in the immediately preceding years, particularly in populations with relatively stable incidence curves.

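### Mandatory survey items cannot prevent abandoned or missed waves, yet the plan dismisses missing data on that ground and analyses only people who answered every questionnaire at all three time points

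*Protocol article*

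**What the plan says.** All references are to the protocol article.

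- **Measurements**, on the survey: missing data are declared to be no problem, "as the survey is conducted through LimeSurvey, where all questions are mandatory and cannot be skipped by participants".
- **Measurements**, next sentence, on who is analysed: "participants must have completed all three measurement points and answered all questionnaires".
- **Data analysis**, on a separate, treatment-based restriction: "Participants who withdraw or fail to complete the treatment will be excluded from the analyses".
- **Data analysis**, on missing values during treatment or follow-up: "The last observation carried forward (LOCF) imputation method will be employed to address missing data". It adds that "sensitivity analyses will be conducted to assess the impact of missing data on the study outcomes".
- **Sample size** assumes 20% dropout within a total of 372.
- **Discussion** warns that the remote format may raise attrition and that "participants may experience fatigue or loss of interest over time".

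**The concern.** The reassurance in Measurements does not follow from its premise. A required field guarantees that a wave, once submitted, has no blanks. It has no bearing on a wave that is never opened or is left halfway, and these are the losses to expect in an unsupervised online survey of 12- to 16-year-olds.

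The inclusion rule then makes a partial loss a total one. Take an adolescent who finishes the game, answers most of the T2 battery and stops before the last questionnaire. That person has not failed treatment, so the treatment-based exclusion need not apply. Under Measurements, however, the person leaves every analysis, including those of instruments fully answered at all three points.

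At stake are outcome data already collected from randomised participants. If stopping is related to fatigue or distress, which is plausible but not documented, the loss is selective and can bias the comparison of arms as well as reduce its precision.

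**Working it through.** **1. Do the sections agree?** Measurements says missing data will not arise as a problem and admits complete cases only. Data analysis provides LOCF and sensitivity analyses for missing data. If only complete cases enter, LOCF has nothing to fill. If LOCF is applied at T2 and T3, people without those waves do enter, and the inclusion rule is not being followed. Both cannot govern the same analysis.

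**2. The plan's own numbers.** The only figures that bear on loss are 372 participants and 20% dropout: 372 × 0.80 ≈ 298. As a check on 372, the precision formula gives 1.96² × 0.25 / 0.05² = 384.1, or 383 after finite-population correction for 90,000. That is 11 above 372, and adding 20% dropout gives 383 / 0.80 = 479. This point does not depend on how 372 was reached.

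**3. Length of a wave.** Item counts are from Assessment tools, Psychological variables:

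- BIP-Q 5 + 1 open item = 6
- KIDSCREEN-27 = 27
- SDQ = 25
- CHASO = 40
- EAQ-30 = 30
- SPSI-R short form = 25
- CD-RISC = 10
- CAG = 48
- Infrequency scale = 12

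The sum is 223 per wave, so 446 over T2 and T3 and 669 over three waves. The clinical and sociodemographic record and the ECODI scale are not counted, so 223 is a minimum.

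**4. Illustrative loss.** Let q be the chance that a respondent permanently abandons the survey at a given item. The document gives no value, so q is **assumed**, constant and independent across items. Loss over k items = 1 − (1 − q)^k.

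| Assumed q | Three waves (k = 669) | T2 and T3 only (k = 446) | T1 only (k = 223) |
|---|---|---|---|
| 0.01% | 6.5% | 4.4% | 2.2% |
| 0.02% | 12.5% | 8.5% | 4.4% |
| 0.03% | 18.2% | 12.5% | 6.5% |
| 0.05% | 28.4% | 20.0% | 10.6% |

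The first column is the strictest reading, with complete cases only. Of 372 it leaves about 348 at q = 0.01% and 266 at q = 0.05%. The second column applies if people who stop at T1 are not counted as randomised losses. The third applies if LOCF fills T2 and T3, since it cannot fill T1. On the strictest reading, the q that alone equals the 20% allowance is 1 − 0.8^(1/669) ≈ 0.033%.

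**5. The same at wave level.** If 1%, 2%, 5% or 10% of participants (assumed) fail to complete each wave, the loss over three waves is 1 − (1 − rate)³ = 3.0%, 5.9%, 14.3% or 27.1%.

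**The case against.** The strongest reply is that losing the participant is an inference.

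- Data analysis plans LOCF, which would keep someone who abandons T2 or T3.
- An adolescent facing an unwelcome item may guess and move on, which costs no wave. The infrequency scale gives some protection against careless answering, although it would not catch a single invented answer.
- The article does not say whether a mandatory item offers an opt-out, whether the survey can be saved and resumed, or whether partial waves are stored. An article may leave such survey-build detail out.
- The abandonment rate has no source, and it is not clear that those who stop at T1 have already been randomised.
- Adding opt-out responses now would mix response formats within the change scores, because recruitment began in September 2024.

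Most of this stands, and it limits the size of the problem and what should be asked for. It does not rescue the two sentences in Measurements. The reassurance remains a non sequitur whatever the survey build, and LOCF can retain people only by overriding the inclusion rule. If it did so for a whole abandoned T2, the participant's T1 scores would stand in for T2 and record zero change, even on instruments actually answered at T2.

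**Conclusion.** The point holds in a limited form. Measurements is wrong to infer from mandatory items that missing data will not matter. Its all-questionnaires condition discards finished instruments along with unfinished ones, and it contradicts the missing-data handling in Data analysis.

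The size is unknown. The range of about 6% to 28% rests on an assumed per-item risk of 0.01% to 0.05%, independence between items, no resumption and strict application of the inclusion rule. Relaxing any of the last three can change the figure, and the alternative columns above are all smaller.

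A reader might infer more, and the document does not support it:

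- *One unanswerable question necessarily costs the wave and then the participant.* Guessing, an opt-out, resumption or LOCF could each prevent that.
- *The plan as a whole ignores missing data.* Only Measurements dismisses it. Sample size, Data analysis and Discussion acknowledge it.
- *Opt-out responses with a uniform 80% scoring rule are required.* Changing response options mid-trial is a trade-off, and 80% fails for short subscales. CHASO has 40 items for 10 skills, so at least one skill has four items or fewer, and one skip there leaves at most 3/4 = 75%. BIP-Q has five Likert items for five subscales, so one skip loses a subscale.

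**What to change.** 1. In Measurements, delete the statement that missing data will not be an issue, and delete the requirement that all questionnaires be answered as a condition of entering the analysis.
2. Keep saved partial responses. Analyse each randomised participant on every instrument completed at each wave, and treat only the unfinished instruments as missing for that wave.
3. Reconcile Measurements with Data analysis: state one rule for who enters each analysis, how the treatment-based exclusion relates to it, and how an instrument missing at a wave is handled.
4. If item-level skips or opt-outs exist, score by each instrument's own missing-item rule.
5. State how the infrequency rule (three or more wrong of 12) applies to a partial wave, since its items are spread through the battery in three groups of four.

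New response options during the trial are optional and not part of this fix.

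**Cost.** Numbers will differ by instrument and must be reported that way. The planned MANCOVA needs all its outcomes together, so it may run on fewer people than the separate ANCOVAs. There is slightly more analysis work, and no change for participants.

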## Materials and methods

### Study design

A clinical longitudinal experimental design with inter-subject comparisons was employed, with the aim of comparing an experimental group (i.e., individuals receiving psychological treatment) and a control group on the waiting list (i.e., those without treatment) at three time points: before treatment (T1), and two post-treatment time points (T2, T3). The control group hasn’t any alternative activities or exposure to placebo-like interactions. Furthermore, an intra-subject analysis was conducted by comparing repeated measures to observe changes within the same individuals before (with pre-treatment measurements, T1), after 6 weeks (T2, in the control group and post-treatment in the experimental group), 6 months after T2 (T3, in the control group and post-treatment in the experimental group).

Initially, immediately after completing the informed consent online, a first evaluation will be conducted for all participants (T1), covering the main areas that constitute the psycho-emotional state of the participants. Following this first evaluation, participants in the experimental group will engage in six weeks of gameplay, with each week dedicated to completing one mission of *emoTICare*. At the six-week mark after the initial evaluation, and immediately following the completion of the *emoTICare* application by participants in the experimental group, a second evaluation (T2) of all participating adolescents (control and experimental groups) will take place. Following a period of six months from T2, a subsequent measurement, designated T3, will be conducted in all participants.

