The primary focus of this study is on the evaluation of the programme’s overall effectiveness, as opposed to the presentation of definitive assertions concerning the outcomes of individual participants. It is imperative to emphasise that the tests are embedded in pre-specified models, with the primary focus being on assessing the overall effectiveness of the programme.

Before testing the change models, descriptive analyses, Pearson correlations, and multivariate and univariate analysis of variance (MANOVA and ANOVA) will be conducted using pre-intervention scores for participants in experimental and control groups to identify potential baseline differences. Furthermore, multivariate and univariate analysis of covariance (MANCOVA and ANCOVA) will be performed to detect changes in post-intervention scores (short-term effect), with pre-intervention scores as a covariate. These analyses will focus on latent variables derived from the composite scores of multiple Likert items, which represent underlying constructs such as emotional symptoms or health-related quality of life. Effect sizes (Cohen’s *d*) for each variable will also be calculated to estimate the magnitude of differences between the experimental and control groups. These analyses will be conducted using SPSS V.28.

To ensure the reliability of the results, we will begin with a series of diagnostic tests and validation procedures. This will include an analysis of residuals to assess the goodness of fit of the model, using residual plots and tests for normality (e.g., Q-Q plots and Shapiro-Wilk test). Homoscedasticity will be evaluated through the Breusch-Pagan or White’s test, and the Durbin-Watson statistic will be used to check for autocorrelation in the residuals. These tests will allow us to ensure that the assumptions of the parametric models are met. Additionally, we will conduct cross-validation (k-fold) to ensure that the model generalizes well to unseen data and is not overfitted. We will also perform outlier detection using Cook’s distance and leverage plots to examine the influence of individual data points on the model.

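### The diabetes-knowledge secondary outcome (ECODI) is timed to the game, which only the experimental arm plays, so as written it yields no randomised between-arm comparison

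*Protocol article*

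**What the plan says.** In the protocol article, Measurements, the secondary outcomes are change in perceived threat of disease, change in diabetes psychoeducation and change in resilience. For the second, "the ECODI Diabetes knowledge scale will be used to assess this variable"; the scale has 25 items scored by right and wrong answers. Directly after that description stands a separate time frame: "Time Frame: Start of the game and during the game".

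Earlier in the same section, three measurement points (T1, T2, T3) are defined under a general frame: "Time Frame: Baseline up to 30 weeks". The section also restricts the analysis to participants who completed all three points and every questionnaire.

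Study design sets the contrast: an experimental group against "a control group on the waiting list (i.e., those without treatment) at three time points". It says that "participants in the experimental group will engage in six weeks of gameplay, with each week dedicated to completing one mission", and that the control group does not have "any alternative activities or exposure to placebo-like interactions". Table 1 shows the emoTICare implementation under the experimental group only.

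Data analysis plans MANCOVA and ANCOVA on post-intervention scores with the pre-intervention score as covariate, hierarchical regression of T2-T1 and T3-T1 change on experimental condition, and Cohen's d "for each variable will also be calculated to estimate the magnitude of differences between the experimental and control groups".

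**The concern.** A measurement anchored to the game has no counterpart in an arm that does not play. If the time frame is followed literally, ECODI is collected in one arm only, and there only while the intervention is under way. Randomisation then does nothing for this outcome.

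At stake is the one listed outcome that tests diabetes knowledge directly, which is what the game's first area sets out to teach. A rise in ECODI among players could come from the game, from sitting the same 25 items again, from six weeks of ordinary diabetes care, or from weaker players leaving before the later readings. A single arm cannot separate these. Since it is listed as a secondary outcome of a randomised trial, readers would expect it to be reported as a comparison between arms.

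**Working it through.** The protocol gives no figure to reproduce here. The check sets the schedule, the exposure of each arm and the planned analyses side by side.

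**1. To which outcome does the time frame belong?** The bracket closes the ECODI paragraph and comes before the line on resilience. The natural reading is that it belongs to ECODI. Resilience (CD-RISC) is described with the other questionnaires under Assessment tools. Attaching a game-bound frame to resilience instead would only move the same difficulty to that outcome.

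**2. Who can be measured at those times?** Per Study design and Table 1, the experimental arm plays for six weeks and the control arm does not play. No section describes later access to the game for controls.

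**3. Is ECODI scheduled anywhere else?** It does not appear under Assessment tools, and no text names it at T1, T2 or T3. The SPIRIT schedule (Fig 1) is not visible, so it can neither confirm nor rule this out.

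**4. What is scheduled for ECODI in the visible text?**

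| Time | Experimental arm | Control arm |
|---|---|---|
| T1 / start of game | yes (start of game) | none stated |
| During the game | yes | not applicable |
| T2 (after the game) | none stated | none stated |
| T3 (six months after T2) | none stated | none stated |

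The game link is given at the end of the T1 survey, so the start-of-game reading may coincide with T1 for players. That gives a baseline in one arm only.

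**5. Can the planned analyses run?**
- Cohen's d between groups needs a score in both arms; there is none for controls.
- ANCOVA needs a post-intervention score with a baseline covariate in both arms; T2 is missing in both and the baseline is missing in controls.
- Regression of T2-T1 or T3-T1 change on condition needs both time points in both arms, and condition would not vary among those measured.

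With equal allocation of 372, about 372/2 = 186 controls are expected, and 0 of them have an ECODI reading scheduled in the visible text. The between-arm contrast is undefined at any sample size.

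**6. What would collection in both arms give?** This is illustrative and does not decide the point. Assume that 372 is the number randomised and that exactly the stated 20% drop out: 372 × 0.8 = 297.6, about 149 per arm. The detectable standardised difference at two-sided 5% and 80% power is about (1.960 + 0.842) × √(2/149) = 2.802 × 0.1159 = 0.325, or 0.326 without the normal approximation. Adjustment for T1 multiplies it by √(1 − r²). With an assumed correlation r = 0.5 this is 0.326 × 0.866 = 0.282; with r = 0.6 it is 0.326 × 0.8 = 0.261. If the per-protocol restriction removes more than 20%, these values rise.

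**The case against.** The strongest reply is that nowhere does the protocol say that controls are not given ECODI. Study design has all participants in both arms assessed at T1, T2 and T3, the completeness rule refers to all questionnaires at all three points, and the arm-by-arm schedule is in a figure that cannot be seen. The bracket may simply be loosely worded. This stands in part: the lack of control data is an inference, and confidence should be moderate. It does not remove the point. If ECODI does belong to the three-wave survey, its own time frame contradicts that and needs correcting.

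A second reply is that an effect can still be estimated, because Study design also plans an intra-subject analysis. A reader might indeed infer that nothing at all can be computed for ECODI. The documents do not support that: a within-arm change in players is available. What is missing is the randomised between-arm effect.

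Third, diabetes knowledge appears in none of the stated hypotheses, and the covariance analyses are said to focus on composites of Likert items, whereas ECODI is scored by right and wrong answers. So ANCOVA may not have been meant for it. That is fair and limits the weight of the point. But ECODI is still a named secondary change outcome, and Cohen's d between groups is promised for each variable.

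Finally, a reader might infer that the in-game readings are taken while the first area is teaching the same material. The text does not say when during the six weeks they fall, so that is not claimed.

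**Conclusion.** The point holds in a limited form. As written, ECODI has a game-bound time frame, and the visible text schedules no control-arm, T2 or T3 score. One of the three secondary outcomes therefore supports no randomised comparison, only an uncontrolled change in players that is mixed with retest and time effects. The alternative is that the all-questionnaires rule is meant to include ECODI, in which case two statements within Measurements conflict. Either way the protocol needs a correction.

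This rests on reading the bracket as belonging to ECODI, on controls having no game access during the study, and on the unseen SPIRIT figure not scheduling ECODI by arm. The primary outcomes and the stated hypotheses are unaffected. Confidence is moderate. The change is worth making because it is cheap, not because the trial's main conclusions depend on it.

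**What to change.** Preferred: replace the ECODI time frame with T1, T2 and T3 in both arms, and add the scale to the LimeSurvey battery. Compare the T2 total, and then T3, between arms with the T1 score as covariate. Keep any in-game readings as a process measure in the experimental arm.

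For participants already past T1 when the change takes effect, collect ECODI at their remaining waves in both arms and compare without baseline adjustment. State beforehand how the adjusted and unadjusted results will be combined. Word the completeness rule so that a missing T1 ECODI does not exclude these participants from the other analyses.

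Cost: a survey edit, a minor amendment and 25 more items per wave for every participant, in a battery that is already long. On the published timeline recruitment runs to April 2026 and data collection to February 2027, so how many participants could still contribute a baseline depends on when the change is made.

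Failing that, relabel ECODI as a descriptive in-game measure of the experimental arm and state that it supports no conclusion on efficacy. This adds no burden but gives up the controlled comparison.

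If ECODI is already collected at T1 to T3 in both arms, correcting the time frame and listing the scale under Assessment tools is enough.
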